## Abstract

**Background:**

Intimate Partner Violence (IPV) is the most common form of violence in conflict and post-conflict settings, but there are few evaluations of interventions to prevent IPV in such settings.

**Methods:**

The Women for Women International (WfWI) intervention is a year-long combined economic and social empowerment intervention for marginalized women survivors of conflict. Primarily, it seeks to support women to achieve four key outcomes: women earn and save money; women improve their health and well-being; women influence decisions in their homes and communities; women connect to networks for support. The organization recognizes Violence Against Women and Girls (VAWG) as a significant barrier to women’s empowerment and expects to see reduction in VAWG, and specifically IPV, as part of building women’s social and economic empowerment. This program is being quantitatively evaluated through an individually randomized control trial amongst women in Afghanistan, with a 24-month follow up. A comparison of baseline characteristics of participants is also included as well as a discussion of implementation of the baseline research.

**Discussion:**

There is a high demand amongst Afghan women for such interventions, and this posed challenges in completing the randomization and baseline. In addition, the complex security situation in Afghanistan also posed challenges. However, despite these issues, recruitment was successfully achieved and the arms were balanced on socio-demographic measures. The evaluation will contribute to the limited evidence base on interventions to prevent IPV in conflict-affected settings.

**Trial registration:**

NCT03236948. Registered 28 July 2017, retrospectively registered.

## Background

In conflict and post-conflict settings, intimate partner violence (IPV) is the most common form of violence that women experience, despite non-partner sexual violence and other forms of violence being more often focused on [1, 2]. There is also increasing evidence that high rates of IPV are likely to continue after conflict has ended [3–7] and are fueled by the enduring impact of conflict [8]. IPV and other violence experienced by women and girls need to be prevented in conflict-affected settings, as much as this must be done in more peaceable contexts.

Until fairly recently, reducing IPV among conflict-exposed populations was not very high on the peace-building or development agenda. As a result, few interventions to reduce IPV have been tested in these settings [1]. The interventions tested have generally combined economic empowerment of women with or without some form of other elements, including gender-focused ones. In conflict-affected communities in Uganda, a women’s economic empowerment intervention showed no impact on IPV experience, but the addition of a short male partner involvement intervention showed some positive (but non-significant) improvements in relationships [9]. Similarly, in Afghanistan, an economic-only intervention showed increases in women’s economic participation and mobility, but showed no impact on women’s status within the home [10]. In post-conflict Ivory Coast, a women’s savings group intervention had gender dialogue sessions added to it, which showed positive trends in outcomes [11]. The positive effects of interventions combining gender transformative/social empowerment components with economic interventions is reflected in the wider IPV prevention research in non-humanitarian settings [12, 13]. More research is needed to develop interventions that are appropriate and effective in challenging contexts.

Afghanistan has experienced more than four decades of conflict and has a deeply patriarchal gender regime based on conservative cultural practices and conservative Islamic interpretations of men’s and women’s roles. Women have very little power, violence against women and girls is endemic, and harmful traditional practices are widespread. These include honour killings, early and forced marriage of girls [14], bride price (*walwar* or *sherbaha*^1^), *baad* (the giving of girls to a disputant party to settle a debt or conflict) and *badal* (women and girls exchanged between families for marriage). Women’s options for leaving abusive relationships are highly constrained: women’s freedom of movement and access to social safety nets are highly limited; and women who ‘run away’ are regarded as having attempted to commit the ‘moral crime’ of *zina* (which implies either adultery or having sexual relations with somebody out of wedlock) regardless of whether there is any evidence or not. Women survivors of sexual violence have also been accused of committing *zina.* If caught, women would be punished either through the formal system (jail) or through informal systems and there have been many reports of women being abused at the hands of mobs. Women have also been subjected in abusive investigatory techniques by the police, including (scientifically invalid) ‘virginity testing.’^2^

The use and acceptability of violence against women and girls in Afghanistan is widespread. The 2015 Afghanistan Demographic and Health Survey (AFDHS) found that 80% of women and 72% of men (for both groups, married and aged 15 to 49) agreed that it was justified for a woman to be beaten by her husband in at least one of five circumstances, particularly if a woman goes out of the house without telling her husband [15]. An early estimate on women’s experiences of IPV in Afghanistan from research conducted with 4700 women in 16 (of 34) provinces found that 73.9% of women reported psychological IPV, 52.4% of women reported experiencing physical IPV ever, and 39.3% of women experienced physical IPV in the previous year [16]. The study found risk factors for experiencing IPV included being in a forced marriage, being in a polygamous marriage, being under age 15 years old and married, having gender inequitable attitudes, and living in a rural area [16].

More recent data from the 2015 AFDHS indicates that 56% of ever married women aged 15 to 49 reported having ever experienced any type of spousal violence (emotional, physical or sexual) and 52% reported having experienced at least one of these forms of violence in the past 12 months [15]. Spousal physical IPV is the most common type of violence, with 51% of women reporting ever having had experienced physical violence (e.g. being slapped, pushed or shaken, punched, kicked, dragged, choked, burned or attacked with a weapon, or having their arm twisted or hair pulled). Of those women having reported spousal physical violence in the past 12 months (45.8%), 26% sustained subsequent physical injuries [15]. Fewer women reported ever having experienced any kind of spousal emotional violence (37%), or sexual violence (7%), though it is likely sexual violence is under-reported. The Afghanistan DHS found a wide range of risk factors for spousal violence, including women being employed but not being paid in cash (i.e. receiving goods or other non-cash earnings), lower education of both women and their spouses, husbands’ controlling behaviour, a family history of domestic violence, and living in a rural area [15]. There was also wide variation by Province in the prevalence of lifetime IPV, ranging from 6% in Helmand province and 7% in Badakhshan Province, to 92% in Ghor and Herat Provinces [14].

This paper describes the methods for an evaluation of an economic strengthening and social empowerment intervention, developed and used for 15 years by the international non-governmental organization Women for Women International (WfWI) in Afghanistan. We report the methods in terms of the SPIRIT (Standard Protocol Items: Recommendations for Interventional Trials) 2013 Checklist [17], and compare baseline characteristics of participants. The trial is an individually randomized control trial with endline follow up 24 months after baseline.

## Methods/design

The trial is conducted as part of the “What Works To Prevent Violence? A Global Programme on Violence Against Women and Girls (VAWG)”, funded by the UK Government’s Department for International Development (DFID).^3^ The Global Programme is funding research on 16 interventions in 13 countries to assess the effectiveness of the interventions in prevention of VAWG. The work is conducted in Africa, the Middle East and Asia.

This trial is being led by the South African Medical Research Council working through local research agencies in Afghanistan, and the intervention is being delivered as per normal practice by WfWI.

### Objectives

The aim of this study is to evaluate the effectiveness of the Women for Women International (WfWI) intervention in reducing IPV experienced by married Afghan women and improving their mental health.The primary objective is to determine whether exposure to the WfWI intervention is effective in reducing experience of intimate partner violence and improving the mental health of women in the programme.The secondary objective it to determine whether exposure to the WfWI intervention is effective in improving women’s income and savings, and creating more equitable gender attitudes, including reducing the acceptability of IPV.

### Trial design

The study is a two-arm, individually randomized controlled trial. Intervention arm participants receive the WfWI intervention (i.e. WfWI’s core programme), a combined social empowerment and livelihoods strengthening intervention, alongside a US$120 cash transfer over 12 months (US$10 per month). This cash transfer is a standard part of WfWI’s core programme to cover training-related expenses, contribute to household needs and help women to start to build savings. Control arm participants are given $10 per interview to motivate assistance in the study and as reimbursement.

### Sample size

A pilot study was conducted in August 2016 with 100 women who were already part of the WfWI intervention to assess the questionnaire, as well as provide an estimate of physical IPV experience in the past 12 months. We found many of the women already enrolled in the WfWI intervention were not currently married, in fact only 37/100 were. Among these, past year physical IPV prevalence was 32.4% and past year severe IPV prevalence was 27%. At the time, this corresponded to published data, which estimated 39.3% of women had experienced past year physical IPV [16].

We used an assumption of seeing an effect size of 0.3 difference between the 12 month prevalence of physical IPV at endline in the control and intervention arms. This is the effect size seen in several recent evaluations of effective violence prevention interventions [18, 19]. We assume that the 12 month control arm IPV prevalence will be 32% and severe IPV 27%. Using Stata, with power set at .80 and alpha at 0.05, sample size per arm was estimated to be 337 for past year physical IPV, and 422 for past year severe physical IPV. Based on our calculations for the percentage of women recruited into the intervention being currently married, and the potential loss to follow-up, the target number of participants was 1477.

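### The planning effect is worded as a 0.3 difference in prevalence, but 337 and 422 per arm come from a 30% relative reduction, so the powered effect is overstated about threefold

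*Protocol article*

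**What the plan says.** The Sample size section of the protocol article sets the planning effect in one sentence: "We used an assumption of seeing an effect size of 0.3 difference between the 12 month prevalence of physical IPV at endline", comparing the control and intervention arms. It adds that effects of this size were seen in several recent evaluations of effective interventions.

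The control-arm values follow: "We assume that the 12 month control arm IPV prevalence will be 32% and severe IPV 27" per cent. The calculation was done in Stata "with power set at .80 and alpha at 0.05", and the result is given as "sample size per arm was estimated to be 337 for past year physical IPV, and 422 for past year severe physical IPV". After inflation for marital status and loss to follow-up, "the target number of participants was 1477".

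The section does not say that 0.3 is a relative or proportional quantity. It gives no intervention-arm prevalence and does not say whether alpha is one- or two-sided. No other section of the article supplies these.

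**The concern.** A difference between two prevalences is, on its ordinary meaning, an absolute difference. A fall of 0.30 from 32% would all but eliminate physical IPV, and a fall of 0.30 from 27% cannot happen. Trials planned around such an effect would need a few dozen women per arm, not several hundred. So the stated effect and the stated sample sizes cannot both be right as written.

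Physical and severe physical IPV are two of the three primary outcomes, and this sentence is the article's only statement of the effect the trial was designed to detect. Taken literally, a fall from 32% to about 22% would look like a third of the target, when it is the target. Readers also cannot compare 0.3 with the cited evaluations, or reuse it in planning, without knowing its scale.

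**Working it through.** **Inputs.** From the Sample size section: control prevalences 0.32 (physical IPV) and 0.27 (severe physical IPV), power 0.80, alpha 0.05, effect 0.3, and stated sizes 337 and 422 per arm. Two inputs are assumed because the article does not state them: a two-sided test, and 1:1 allocation (the Trial design section describes two arms, and a single per-arm figure is given for each outcome).

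**Formula.** Pooled-variance comparison of two proportions, without continuity correction:

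n per arm = [z₁·√(2p̄(1−p̄)) + z₂·√(p₁(1−p₁) + p₂(1−p₂))]² / (p₁−p₂)²

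with p̄ = (p₁+p₂)/2, z₁ = 1.960 and z₂ = 0.842.

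**Step 1: reproduce the stated sizes, reading 0.3 as a 30% relative reduction.**

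- Physical IPV: p₁ = 0.32, p₂ = 0.70 × 0.32 = 0.224, p̄ = 0.272. The numerator is (1.960 × 0.6293 + 0.842 × 0.6256)² = 3.0975 and the denominator is 0.096² = 0.009216, so n = 336.1, rounded up to **337**.
- Severe physical IPV: p₁ = 0.27, p₂ = 0.70 × 0.27 = 0.189, p̄ = 0.2295. The numerator is (1.960 × 0.5947 + 0.842 × 0.5919)² = 2.7681 and the denominator is 0.081² = 0.006561, so n = 421.9, rounded up to **422**.

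Both match exactly. Power at these sizes is 80.1% and 80.0%.

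**Step 2: read 0.3 as an absolute difference, as worded.**

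- Physical IPV: p₂ = 0.32 − 0.30 = 0.02, p̄ = 0.17. The numerator is (1.960 × 0.5312 + 0.842 × 0.4870)² = 2.1056 and the denominator is 0.30² = 0.09, so n = 23.4, rounded up to **24**. At 337 per arm, power would be essentially 100%.
- Severe physical IPV: p₂ = 0.27 − 0.30 = −0.03, which is impossible.

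**Step 3: other readings of 0.3.**

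| Reading | n per arm, physical | n per arm, severe |
|---|---|---|
| Stated in the article | 337 | 422 |
| 30% relative reduction, two-sided | 337 | 422 |
| 30% relative reduction, one-sided | 265 | 333 |
| 30% relative reduction, two-sided, continuity-corrected | 357 | 447 |
| Absolute difference 0.3, two-sided | 24 | impossible |
| Absolute difference 0.3, two-sided, continuity-corrected | 30 | impossible |
| Cohen's h or d = 0.3 | 175 | 175 |
| Odds ratio 0.7 | 611 | 687 |
| Log odds ratio 0.3 | 853 | 955 |

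Of the readings tried, only the two-sided 30% relative reduction without continuity correction gives both stated figures.

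**Step 4: size of the misstatement.** The absolute differences behind the stated sizes are 32.0 − 22.4 = 9.6 points and 27.0 − 18.9 = 8.1 points. The worded difference exceeds them by 0.30/0.096 = 3.1 and 0.30/0.081 = 3.7.

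**Step 5: the same effects as odds ratios.** (0.224/0.776)/(0.32/0.68) = 0.61 and (0.189/0.811)/(0.27/0.73) = 0.63.

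**The case against.** The best case on the other side is that this is loose wording and nothing in the design is wrong. The sizes of 337 and 422 are right for a 30% relative reduction, and the target of 1477, the power and the analysis are unaffected. The text does not use the word absolute or speak of percentage points. The same paragraph rules out the absolute reading, so a careful reader can recover the meaning from the five numbers given. No success criterion in the article refers to the 0.3; the primary analysis simply fits a mixed model with a treatment term.

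Much of this stands. The error is in how the effect is stated, not in the calculation, and no decision rule of the trial turns on it. The figures can be reproduced once the scale of the 0.3 has been guessed. It is also true that two-sided alpha is inferred from the match rather than stated.

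It does not remove the point. The sentence does specify a scale, a difference between prevalences, and that scale contradicts the numbers beside it. The right one can be found only by solving backwards from the sample sizes, and the candidate readings run from 24 to 853 per arm for physical IPV.

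**Conclusion.** The concern holds. The stated planning effect is wrong as written: the trial is powered for a prevalence ratio of 0.70, which is 9.6 points for physical IPV and 8.1 points for severe physical IPV, not for a difference of 0.3. The overstatement is 3.1-fold for physical IPV, the outcome the sentence names, and 3.7-fold for severe physical IPV. The sample sizes themselves are correct.

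This rests on 1:1 allocation, a two-sided test and the pooled-variance formula. None of these is stated in the article, but together they reproduce both figures exactly. Whether the cited evaluations reported a 30% relative reduction cannot be checked from the document, and nothing here depends on it. The correction should be made because the target effect is the yardstick for reading two of the three primary outcomes.

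**What to change.** Replace the effect-size sentence in the Sample size section with wording such as:

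> The calculation assumed a 30% relative reduction in prevalence (prevalence ratio 0.70): from 32.0% to 22.4% for past year physical IPV (9.6 percentage points; odds ratio 0.61) and from 27.0% to 18.9% for past year severe physical IPV (8.1 percentage points; odds ratio 0.63), with two-sided alpha 0.05.

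The authors should confirm from their Stata record that the test was two-sided. They should also confirm that the cited evaluations support 0.3 on the relative scale, since the article offers them as its justification. The odds ratios are optional, but useful if the mixed models for the binary outcomes report on that scale.

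The cost is one sentence. The sizes per arm, the recruitment target and the analysis stay as they are.

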### Study setting

The provinces and districts selected for the research were those in which WfWI planned to work in 2016 and 2017 during the recruitment phase. These were established in enrollment plans for the intervention designed at the start of each year, and the research was fitted in around these plans. As per previous years of implementation in Afghanistan, communities in which WfWI implemented their programming were selected through community level assessments, and coordination with district government authorities, to ensure the most appropriate communities would be included. Security concerns also factored into selection of communities, with the aim of ensuring security for WfWI staff members as well as the intervention participants. Due to the introduction of the RCT in 2016, additional criteria for community selection included ensuring a sufficient number of women were eligible to enroll in both the intervention and control arms of the study.

The evaluation was conducted in two provinces, Kabul and Nangarhar. In Kabul, three districts were selected and in Nangarhar, two districts. WfWI was working in additional provinces at the time but we chose to work in two provinces for the study design for pragmatic reasons. In each district, a central village was identified with a training centre from which WfWI could run the intervention. Depending on the size and structure of the village, women also came from surrounding areas.

### Recruitment

Once communities are selected by WfWI, WfWI field staff undertook community mobilization activities to explain the objectives of the programme and the research to community and religious leaders and obtain their support for implementation. Information was then shared in villages through community meetings and Friday Mosque prayers. Women interested in participating were asked to assemble on a scheduled date and location.

Women were individually recruited into the study. WfWI staff members explained WfWI’s core programme, while research staff members explained the research study and randomization process. Participants were screened for eligibility before being enrolled into the study.

### Eligibility criteria

The eligibility criteria for the study mostly followed the entry criteria for WfWI. The regular selection criteria for the WfWI intervention were that participants should be at the lowest economic level possible, earning less than a US$1.25 a day, they should be unemployed, not in school and not involved in a similar programme. Women incapacitated due to mental illness or very severe disability would not be eligible for the intervention, as they otherwise would not be able to fully benefit by engaging in the training sessions (e.g. if blind they would be unable to observe the training materials, or if deaf they would be unable to hear the content of the training) or by doing income generating work. Women should be willing to participate in the programme and attend all training classes and not have previously participated in the programme. Preference was given to women who are mothers or heading households, irrespective of marital status. Women were encouraged to secure support from family members for their involvement to better facilitate their participation, although this was not always possible.

Two additional criteria due to the research were added: 1) restricting the age of women to 18 and 45 years due to issues of consent for those under 18 year olds; and 2) increasing the proportion of currently married women in the sample than is general WfWI practice because in Afghanistan, it is only feasible to ask IPV questions of currently married/previously married women. The age restriction also reduced the likelihood of mother-in-laws being recruited into the study alongside their daughter-in-laws. (A pilot study found that having two members of the same household in the study led to concerns about maintaining privacy about the study).

### Intervention

The intervention has been developed and refined since 1993 by WfWI and is an approach to intervening in complex settings in alignment with the needs of women who have been denied access to education, have been negatively affected by conflict and who seek inclusion and recovery., also referred to as WfWI’s core programme, has been implemented by WfWI in eight countries***.*** The theory of change for the intervention is shown in Fig. 1 and is focused specifically on reducing IPV.

**Fig. 1 Fig1:**
[figure not shown]
Theory of Change: Women for Women International Programme, specifically for IPV reduction

In all the villages, activities are delivered by locally hired staff from the community who speak local dialects. Staff use a range of methods to deliver the curriculum including storytelling, role-playing, or discussion questions. Due to the typically very low levels of literacy of participants in Afghanistan, trainers and staff tend to use verbal methods. Sessions are approximately 90 min long, delivered over a year, to adapt to women’s availability and constraints on their time (such as care work).

Component 1: Informational Training: critical information about savings, health, rights, and networking is delivered through key modules as part of the year-long programme:The value of women’s work: This module focuses on supporting women to overcome stereotypes and inequities that prevent them from gaining economic self-sufficiency. This module educates women about division of labour, household financial management, and the different types of opportunities for income generation that are available to them.Health, wellness and violence against women. This module focuses on building women’s understanding of: health as an asset; health as a human right; health as an essential criterion to undertake other productive activities; women’s bodies and how to care for them; prevention, treatment, and management of key health issues; safe space to discuss sensitive topics, including conflict, sexual and gender based violence; and referrals to health services.Rights, family and community decision-making. This module covers human and legal rights, and what women as individuals- and as a group - can do to exercise their own rights in their families and communities. It addresses women and family law including inheritance, control of assets, marriage, divorce and child custody, and domestic violence and rape.Social networks and safety-nets. This module covers the value of women working together in groups and/or in social networks; building effective networks; planning for group advocacy; managing leadership issues; negotiation and conflict management (within the household).

Component 2: Skill Building: the sessions that fall under skill building are delivered through hands-on training and practice over the year-long programme and focus on building basic skills in:Numeracy. This is provided for women who need it so that women can learn to count, add/subtract, and use money. All women participants in Afghanistan receive this component.Basic business skills. Women learn and practice basic business skills needed for self-employment, group businesses or employment. It covers bookkeeping, selling, planning and marketing their products, and is followed by three sessions on cooperatives looking at the benefits and different types of cooperatives including their structures.Vocational skills. WfWI conducts market assessments to identify the best income generation activities for women, given their resources, education and other constraints. Specific training in Afghanistan is focused on animal husbandry, tailoring, gardening and knitting.

Component 3: Resource provision: To complement the informational training and skill building, women receive financial support, referrals and opportunities for saving through the 12 months:Women receive a monthly conditional cash transfer of US$10 per month (total received US$120). There is no stipulation about how women should spend this month. Some women choose to save this money to help them establish their own businesses. Others use it to cover basic needs such as food, clothing and medicine.WfWI provides women participants with a range of referral services. A list of referral services is developed. Where women need additional support, they are referred through to services.In Afghanistan, WfWI has introduced an adapted version of the Self-Help Group, an informal grouping of women who set up a small ‘bank’ in which they save together. This is not a compulsory savings programme, but many groups decide to start them as part of the programme.

Component 4: Connections to other women, local women’s networks and global supporters: Women go through the programme in classes of 25 and begin the programme with the same group with whom they graduate. This provides a safe space for socially excluded women to learn new skills, share experiences and receive support.

Women for Women International also runs a range of complementary programmes to promote sustainable change and a supportive, enabling environment for women.

Men’s engagement activities: Recognising how women’s participation and ability to affect change in their lives is often shaped by men in the household and at the community level, WfWI has developed a men’s engagement programme (MEP). The goal of the programme is to work with men and male opinion leaders to change gender attitudes and generate an openness to new ideas, such that it is possible to implement the WfWI intervention with women. In Afghanistan, this is a 24 session intervention with male religious and community leaders over three months. The focus of this training is on family rights in Islam. Selected graduates of this programme are then trained to lead “stepdown” discussion groups with men in their local communities to discuss issues around women’s rights, multiplying the reach of the initial training. The men discuss topics that affect their communities and their daily lives. The curriculum is underpinned by Islam, quoting verses from the Qur’an to underscore specific aspects of women’s rights.

The MEP is being implemented in one of the six villages for the trial as per the practice of WfWI to selectively implement the MEP in selected communities on a case-by-case basis. Through the community assessment process, WfWI find some communities show resistance to WfWI’s core programme. WfWI prioritizes those communities for the MEP intervention, as a strategy to reduce resistance and enable support for the programme.

